**Methods:**

The engAGE platform was built around the social robot Pepper, which provides cognitive therapy. An activity tracker and a mobile app were also integrated within the platform to help older adults with MCI monitor their sleep and physical activity, in addition to offering cognitive games at home. The proof of concept (PoC) of engAGE was designed as a 6-month long randomized controlled trial (RCT) aimed to test the solution in three European countries: Italy, Switzerland, and Norway. During this period, under the supervision of a psychologist or a therapist, Pepper provided cognitive therapy on a weekly basis at health care or daycare facilities. In parallel, the use of the mobile app and the activity tracker was recommended on a daily basis. Participants were recruited through health care institutions and care organizations and evaluated through face-to-face interviews. The primary interest of the study was to assess the impact of engAGE on cognitive capacity through the Montreal Cognitive Assessment (MoCA) and the Memory Assessment Clinic Questionnaire (MAC-Q). In addition, changes in social engagement and quality of life were measured through the University of California, Los Angeles (UCLA) Loneliness Scale and the Warwick-Edinburgh Mental Well-Being Scale (WEMWBS). The PoC also focused on the acceptability and usability of engAGE, evaluated through the System Usability Scale (SUS) and the Unified Theory of Acceptance and Use of Technology (UTAUT) questionnaire. In addition, data were collected regarding the frequency of weekly sessions and access to the mobile app, as well as activity tracker measurements.

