#### The Social Robot Service

As the social robot service, the Android version of Pepper’s tablet offers dashboards for cognitive games, storytelling, and activities to the end user through an easy-to-use interface. Equivalent cognitive games are also integrated into the communication service to allow the end user to play them on the tablet at home. Pepper is a humanoid social robot able to dialogue with the user by speaking, moving, and expressing emotions, being also equipped with an Android tablet placed at its chest. The user logs through the tablet at every session and then interacts with the robot and plays the planned activities (drama play or cognitive games). To track the user’s progress, each performance is recorded, and scores are sent to the cloud, along with the user ID. As the sessions are held in groups of 4 or 5 older adults, the users can choose to play individually or in teams. Once the type of game is selected, the user is redirected to a new screen in which all the games corresponding to the type selected is displayed. When the user plays and succeeds in a task, the robot congratulates them. To ensure that the user understands the robot, the words the robots says are displayed on the screen like subtitles. The interaction is recommended to be vocal as much as possible to improve the user experience. Different categories of cognitive games and storytelling activities are implemented in the service. The games are and will be iteratively developed and included in the service in the different versions of the prototype while considering end users’ feedback:

Familiar games: crosswords, memory cards, and remembering objects that appearQuizzes: picture, musical, and cultural quizzesStory-/play-telling: story listening, poem recitation, and YouTube shorts, with questions asked about the activity

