#### The Experimental Group

The EG used the engAGE system in two different settings: at health care organizations and at home. For the Italian site, the health care organizations were the Neurology Unit and Alzheimer Assessment Unit (Memory Clinic) and the Alzheimer daycare center of the IRCCS INRCA. Weekly sessions were run at the IRCCS INRCA usability lab (YOUSE) in the hospital. For the Norwegian site, weekly sessions were managed at Solhaug and Plankemyra in the city of Arendal. For the Swiss site, the participants (primary end users) attended weekly sessions at the Hôpitaux Universitaires de Genève’s (HUG) living lab. At the health care organizations, the primary end users interacted with Pepper. The interaction was supervised by tertiary end users (formal caregivers, ie, occupational therapists, psychologists, or psychotherapists) and included the following activities: dialoguing with the robot, storytelling, drama play, and cognitive and physical games. The human-robot interaction was planned to last about 1 hour and to be scheduled once a week for 6 months. At home, the older adults interacted with the tablet, supervised by informal caregivers (relatives). In addition, the primary end users played cognitive and physical games installed on the MEMAS app. This activity was suggested to be performed for 30 minutes every day for 6 months. Throughout the entire period of experimentation (unless they decided otherwise), the older adults wore the smartwatch for measuring their physiological parameters and steps. Any activity performed by them was assigned by formal caregivers and could be personalized, considering the primary end users’ abilities (difficulty levels of the games), lifestyle (reminding and monitoring services), and social interactions. Before starting the PoC, one session was dedicated to primary end users to teach them how to use the activity tracker and the MEMAS app at home. During weekly sessions, they were allowed to ask for clarifications about the use of these devices, and they could receive remote support from technicians during the week if any problem occurred.

Figure 2 shows the scheme of the intervention for the EG.

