### Data Analysis

This subsection describes the measurements, statistical tests, and tools with which the data collected in the engAGE PoC were, and are still being, analyzed. The different types of data that were collected in the engAGE project are as follows:

Credentials: username, password, email address, and similar security information used for authentication and account access in different services of the platformPersonal data: first name, last name, gender, age, weight, height, email address, contact address, and phone number of older adults in different services of the platformAnswers to specific questions in self-assessment questionnaires on MEMASGames score from Pepper appsMeasurements and monitored parameters: weight, heart rate, blood pressure, and physical activities gathered through the monitoring infrastructureHistorical data of the measurements and monitored parameters for training and using ML algorithms for each older adult in the ML service

In the engAGE testing and evaluation phase, the following data were, and are being, processed:

Information and results from questionnairesCognitive game scoresHistorical data of measurements collected for each end userAny information the end users decided to share through discussions/interviews, as well as data providing feedback from trialsOutcomes that concern feasibility (ie, the primary interest of the engAGE PoC): recruitment rate (proportion of eligible individuals who consent to participate in the study, ie, those who attended more than 80% of weekly sessions), retention rate (proportion of participants who completed the 6-month intervention period), and adherence to the intervention (average number of interactions with the Pepper robot during weekly sessions, the frequency of use of the MEMAS app, and the activity tracker recording time)

Descriptive statistics (means, SDs, medians, IQRs) will be used to summarize adherence metrics.

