Outcomes that concern efficacy of the engAGE intervention were considered exploratory and dealt with the metrics about cognitive capacity, quality of life, social dimension, and stress and care load relief (for caregivers). In particular, to explore the potential efficacy, changes in these domains before and after the intervention were analyzed. Paired *t* tests (for normally distributed data) or Wilcoxon signed-rank tests (for nonnormally distributed data) were used to compare pre- and postintervention scores within each group, while independent samples *t* tests or Mann-Whitney U tests were performed to assess between-group differences in change scores. Moreover, effect sizes (Cohen d or Cliff δ) were calculated to quantify the magnitude of any observed differences. Due to the nature of the PoC, this study was not powered to detect statistical significance. *P* values will be reported without adjustments for multiple comparisons and interpreted with caution. All analyses were planned for descriptive purposes, and only participants with at least 80% of adherence to the intervention were considered for analysis.

The aforementioned analyses were also applied to acceptance and usability measurements (ie, UTAUT and SUS scores) that provided insights into the primary goal of the study: the feasibility of the intervention. Data from the ML service were analyzed to correlate physical activity, sleep parameters, game scores, and self-assessment data. Longitudinal data analysis techniques (eg, mixed effects models) were used to analyze changes in these parameters over time and assess potential correlations with cognitive and quality-of-life outcomes.

The first step in the data analysis dealt with the description of the sample. Continuous variables will be reported as either the mean (SD) or the median (IQR) on the basis of their distribution (assessed using the Kolmogorov-Smirnov test). Categorical variables will be expressed as an absolute number and percentage. Mann-Whitney U tests (for nonnormal distribution) or chi-square tests (for normal or nonnormal distribution) were used to compare independent and dependent variables between the pre- and postintervention conditions, in addition to simple descriptive statistics (means, medians, and SDs, as appropriate).

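### Adherence to the weekly robot sessions is measured by an interaction count that can stay flat or rise as attendance falls, and the 80% adherence rule cannot be computed from it

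*Protocol article*

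**What the plan says.** The Data Analysis section of the protocol article lists recruitment, retention and adherence as the feasibility outcomes and calls them the main interest of the study. Adherence has three measures. The first is the "average number of interactions with the Pepper robot during weekly sessions"; the others are "the frequency of use of the MEMAS app, and the activity tracker recording time". Only the first concerns the sessions at the facility. It is a count, with neither a number of scheduled sessions as denominator nor a target.

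Two sections describe the sessions:
- The Social Robot Service: "As the sessions are held in groups of 4 or 5 older adults, the users can choose to play individually or in teams".
- The Experimental Group: "The human-robot interaction was planned to last about 1 hour and to be scheduled once a week for 6 months".

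Attendance appears in other places:
- The recruitment rate in Data Analysis is qualified by "those who attended more than 80% of weekly sessions".
- The Methods paragraph of the abstract says that "data were collected regarding the frequency of weekly sessions and access to the mobile app".
- The Social Robot Service section says "The user logs through the tablet at every session".

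Table 1 gives an ad hoc questionnaire as the tool for adherence. Later in Data Analysis the analysis set is restricted: "only participants with at least 80% of adherence to the intervention were considered for analysis". The text does not say what the 80% is a percentage of.

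**The concern.** An adherence measure should go down when people stop coming. A count of robot interactions need not. If several people share one robot for an hour, an absence frees turns for those who are there. A count averaged over the sessions a person attended leaves out the missed ones altogether.

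Three things are at stake. Adherence is one of the outcomes on which feasibility will be judged. The Limitations section says the findings should help to refine the intervention protocol for later studies, so an attendance shortfall that the measure does not show could carry forward. And the analysis set is defined by an 80% adherence rule, which needs a quantity with a known 100%.

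**Working it through.** The article gives no figure for this measure, so there is nothing to reproduce. The check asks how the measure behaves when attendance falls.

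**Inputs from the article.** Group size g = 4 or 5; sessions of about an hour, weekly for 6 months, or about 26 sessions.

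**Assumptions, not in the article.**
- One robot per session (implied, not stated).
- K = 40 interactions possible in a session. The ratios do not depend on K.
- Members attend independently, each with probability a.
- Those present take up a share s of absentees' turns: s = 1 means robot time is always fully used, s = 0 means turns per person are fixed.

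**Formulas.** The chance that anyone attends is 1 − (1 − a)^g.
- Full take-up, per attended person-session: K[1 − (1 − a)^g]/(g·a).
- Full take-up, per enrolled person per scheduled session: K[1 − (1 − a)^g]/g.
- No take-up: K/g per attended session and a·K/g per scheduled session.
- Half take-up is midway between these.

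**Numbers, g = 5.** At a = 0.6, 1 − 0.4^5 = 0.98976. Full take-up then gives 40 × 0.98976/3 = 13.2 per attended session and 40 × 0.98976/5 = 7.92 per scheduled session.

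| Averaged over | Take-up | 100% attend | 80% attend | 60% attend |
|---|---|---|---|---|
| attended sessions | full | 8.0 | 10.0 | 13.2 |
| attended sessions | half | 8.0 | 9.0 | 10.6 |
| attended sessions | none | 8.0 | 8.0 | 8.0 |
| scheduled sessions, group mean | full | 8.0 | 8.00 | 7.92 |
| scheduled sessions, group mean | half | 8.0 | 7.20 | 6.36 |
| scheduled sessions, group mean | none | 8.0 | 6.4 | 4.8 |

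Groups of 4 behave alike. With full take-up the attended-session score goes 10.0, 12.5, 16.2 and the scheduled-session score 10.0, 9.98, 9.74.

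**Attended-session average.** In this model the score never falls with attendance. The factor [1 − (1 − a)^g]/a equals 1 + (1 − a) + … + (1 − a)^(g−1), which grows as a falls; with no take-up the score is constant. At 60% attendance and full take-up it is 13.2/8.0 = 1.65 times its starting value.

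**Scheduled-session group mean.** With full take-up it hardly moves. With half take-up a 40% loss of attendance shows as 1 − 6.36/8 = 20.5%. It falls in proportion only with no take-up.

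**One participant.** Suppose one person attends 80% or 60% while the others always come. With missed sessions scored zero, the score is 0.8 × 8 = 6.4 or 0.6 × 8 = 4.8, in proportion to attendance even with full take-up. Averaged over attended sessions it stays at 8.0. Likewise, someone at 5 of 26 sessions with 8 interactions each scores 8.0 per attended session, the same as someone at all 26, but 5 × 8/26 = 1.5 per scheduled session.

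**The 80% rule.** An attendance proportion has a natural 100%: 0.8 × 26 = 20.8, so at least 21 of about 26 sessions. The interaction count has no stated maximum or target, so there is nothing to take 80% of.

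**Linkage.** Safety and Security Considerations calls the retained robot interaction counts anonymous, which puts a per-person score in further doubt. The Social Robot Service section, by contrast, sends scores to the cloud with a user ID.

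**The case against.** The strongest case on the other side has five parts.

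- **Condensed article.** Whether an average runs over attended or scheduled sessions is often left to a fuller document. That is fair, and the missing denominator alone would not be a finding. But the article does fix the quantity as an interaction count, and with shared turns a scheduled-session denominator repairs the group mean only if absentees' turns are not taken up.
- **Attendance is recorded elsewhere.** The abstract, the recruitment-rate clause and the login all show this, and retention would reveal people who leave for good. This stands, and it limits the harm. However, none of these is named as the adherence measure, and the only attendance threshold sits inside the recruitment rate.
- **Another meaning of interaction.** The Experimental Group section uses the word for the whole hourly encounter. A count of encounters would follow attendance. The phrase in Data Analysis, which places interactions within sessions, fits a count of turns better, but the other reading is possible.
- **The low attenders may be excluded.** If the 80% rule refers to attendance, people at 60% would not be analysed. The text does not say that it does.
- **Assumed inputs.** Capacity, take-up and independence are not in the article, and neither is how a team turn is counted. The figures are illustrations only.

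A reader might go further and infer that the score must rise or stay flat as attendance drops, so that it does not measure adherence at all. The article does not support that. It fixes neither the denominator nor the take-up, the score falls under some readings, and the count is one of three adherence measures. Nor does it follow that poor attendance will necessarily be reported as good engagement.

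**Conclusion.** The point holds in a limited form. As stated, the measure of session adherence cannot be relied on to show attendance. In the illustration, a fall to 60% attendance moves the score anywhere from a 65% rise (13.2 against 8.0) to a 40% fall (4.8 against 8.0), depending on two things the article leaves open: the denominator and the take-up of absentees' turns. Separately, and without any of those assumptions, the 80% adherence rule cannot be computed from a count that has no stated full value.

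The size rests on one robot per session, independent attendance and the assumed take-up shares; the value of 40 interactions does not affect the ratios. The model also assumes that nobody takes fewer turns because others are absent. Adherence is reported descriptively and no success threshold is attached to the count. The consequence is a feasibility figure that may mislead and an analysis set that is not reproducible from this component, not a wrong test result.

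**What to change.** In Data Analysis, define adherence to the weekly component as sessions attended divided by sessions scheduled for that participant. Take attendance from the login at each session and the session-frequency data. State that any use of 80% for this component, including in the rule for the analysis set, refers to that proportion, and move the attendance clause out of the recruitment rate. Report interactions per attended session separately as a description of intensity of use, with the number present and whether play was individual or in teams where that was recorded. Align the adherence row of Table 1.

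The cost is small: a changed definition, using data the article says were collected, provided the logins were kept by participant. The adherence figure may be less favourable. The article says data analysis is complete but results are unpublished, so the redefinition should be disclosed as made after data collection, with the interaction average still shown beside it.

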### Study Design

The PoC was structured as a controlled longitudinal pilot study, with a before-and-after design, where observations were run on a series of enrolled individuals, who received the intervention described later, with data collected before and after the installation and use of the technical solution. The goal of trial evaluation was to demonstrate the viability of engAGE technology integration into everyday life to counteract cognitive decline. As secondary outcomes, the impact on the social dimension and quality of life of end users was evaluated. Moreover, acceptance over 6 months and the usability of proposed solutions were evaluated to understand the feasibility of the intervention. Despite the choice to structure the PoC as an RCT in order to provide more robust evidence on feasibility and efficacy [22,23], a formal sample size calculation was not performed. Practical constraints within the project were considered while deciding the number of end users to enroll. In fact, recruitment timelines, availability of rooms and professionals, and technical equipment represented practical limits for the study feasibility. After considering these constraints, the sample size for the PoC was set to 80 primary end users: 50 (62.5%) in the experimental group (EG) and 30 (37.5%) in the control group (CG).

In Italy, end users were recruited from the Neurology Unit and Alzheimer Assessment Unit (Memory Clinic) and from the Alzheimer daycare center of the Istituto di Ricovero e Cura a Carattere Scientifico – Istituto Nazionale di Riposo e Cura per Anziani (IRCCS INRCA). The research team could communicate with potential participants of previous projects and initiatives, as well as with other people who might have been be interested in contributing to the project evaluations. This method made it possible to be in contact with clients met before and with whom a relationship of trust was already established.

In Norway, participants were recruited from two daycare and housing centers in the city of Arendal. The first one, Solhaug, is a daycare center for old residents living in their own homes, while the second one, Plankemyra, is a combined housing and daycare center.

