### Recruitment

A specific number of people were recruited for the study via health care institutions or health care organizations. Potential participants were evaluated by eligible professionals through face-to-face interviews to verify that eligibility criteria were met. Those who did not meet the criteria or declined participation were excluded. The remaining participants were randomly assigned to the EG or the CG. A randomization technique, conducted by a statistician, based on a single sequence of random assignments was adopted. A list of random numbers was generated by the computer, while subjects were assigned a number based on their order of inclusion in the study. According to this technique, in Italy and Switzerland, the 30 subjects were randomly assigned to one of the two study groups (n=20, 66.7%, in the EG and n=10, 33.3%, in the CG), while in Norway, 20 subjects were equally assigned to the two groups. Next, for both groups, we took careful note of who were lost to follow-up, who discontinued intervention, or who were excluded from analysis. The procedure adopted is summarized in Figure 3.

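### Allocation ratio differs by country, but the between-arm tests on change scores neither stratify by country nor condition on baseline

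*Protocol article*

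**What the plan says.** Recruitment in the protocol article describes randomisation "based on a single sequence of random assignments was adopted", yet gives arm sizes that are fixed by country. For Italy and Switzerland they are "n=20, 66.7%, in the EG and n=10, 33.3%, in the CG", "while in Norway, 20 subjects were equally assigned to the two groups". Study Design gives the planned total as 80, with 50 in the EG and 30 in the CG, and states that "a formal sample size calculation was not performed".

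For efficacy, Data Analysis compares the arms with independent-samples t tests or, for non-normal data, "Mann-Whitney U tests were performed to assess between-group differences in change scores", and adds Cohen d or Cliff delta. No country stratum, site term or baseline covariate is named for this comparison. Mixed-effects models are mentioned only for the parameters handled by the machine-learning service and their correlations with outcomes.

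The same section calls efficacy exploratory and the analyses descriptive. Limitations says that the three countries differ in culture and health care, and that the findings should feed into future sample size calculations. Results says that trial dates differed by country and that 40 participants were assigned to the EG and 9 to the CG.

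**The concern.** When the allocation ratio varies between strata, randomisation within each stratum balances the arms there but not in the pooled sample. The pooled arms then differ in country mix by design, and any country difference in mean change enters the estimated treatment effect. The document gives reasons why such a difference could exist: different recruitment channels, care contexts and calendars.

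The second part concerns efficiency. A T0 score is collected, but the change-score test fixes its coefficient at 1 instead of estimating it, which gives up precision in a very small trial.

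At stake is less the P value, which the article already tells readers to treat with caution, than the effect sizes that are meant to inform the next trial.

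**Working it through.** **1. Reproduce the plan's figures.** Reading the 30 subjects as 30 in each of Italy and Switzerland:
- EG = 20 + 20 + 10 = 50
- CG = 10 + 10 + 10 = 30
- Total = 80, which agrees with Study Design.

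**2. Country mix by arm.**

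| Country | Share of EG | Share of CG | Difference |
|---|---|---|---|
| Italy | 20/50 = 40.0% | 10/30 = 33.3% | +6.7 points |
| Switzerland | 20/50 = 40.0% | 10/30 = 33.3% | +6.7 points |
| Norway | 10/50 = 20.0% | 10/30 = 33.3% | −13.3 points |

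**3. Bias of the pooled difference.** Let D be the mean change in Norway minus the average of Italy and Switzerland, in within-country SDs of change, with no treatment effect. Expected EG minus CG difference = (0.200 − 0.333) × D = −0.133 × D. If Norwegian participants change less favourably than the others, the bias favours the EG; if more favourably, it runs against the EG. D is an assumption; the documents give no value. The standard error at 50:30 is √(1/50 + 1/30) = 0.231 SD.

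| Assumed D | Bias (SD) | Bias / SE | Type I error, unadjusted |
|---|---|---|---|
| 0.25 | −0.033 | 0.14 | 5.0% |
| 0.5 | −0.067 | 0.29 | 5.5% |
| 1.0 | −0.133 | 0.58 | 6.2% |
| 1.5 | −0.200 | 0.87 | 6.8% |

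The last column comes from 40,000 simulated trials per row (two-sided 0.05, which is also an assumption, since the article states no alpha). Adding a Norway indicator to a linear model brought the mean bias to within 0.003 SD of zero and the type I error to 4.9–5.2%.

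**4. Realised numbers.** The planned ratios imply at least one control in three participants, so 49/3 ≈ 16 or more controls would be expected; there were 9. The planned weight of 0.133 therefore cannot be carried over. The country split of the 40 and the 9 is not reported. Purely as illustration, five Norwegians in each arm would give a weight of 5/9 − 5/40 = 0.43, while equal Norwegian shares in both arms would give zero.

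**5. Baseline.** With equal pre and post variance (set to 1) and correlation rho, the change score has variance 2(1 − rho) and the ANCOVA residual has variance 1 − rho². The ratio is (1 + rho)/2:
- rho 0.3: 0.65
- rho 0.5: 0.75
- rho 0.7: 0.85
- rho 0.8: 0.90

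The correlation is not given, so these are a range. Entry criteria restrict MoCA to 21–25 and MAC-Q to 25 or more. If those scores serve as baseline, their variance is cut to some fraction t while the follow-up variance is not cut in the same way. With slope b the ratio becomes (1 + b)/((1 − b)t + (1 + b)). At b = 0.5 this is 1.5/1.75 = 0.86 for t = 0.5 and 1.5/1.65 = 0.91 for t = 0.3. The saving is then 9–14% instead of 25%.

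**The case against.** The strongest reply is that the issue is small and its context disclosed. For D up to 0.5 SD the bias is under a third of a standard error and the type I error stays at or below about 5.5%. Efficacy is labelled exploratory, the article says the trial was not powered, and covariates are often left to an SAP, which is not shown. This limits the seriousness but does not remove the point. The article does not leave the method open: it names tests that do not match the allocation it describes. An exploratory label covers low power; it does not cover avoidable bias in effect sizes intended for planning.

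A reader might infer more than the documents support:
- **That treatment is confounded with country outright.** Every country was planned with both arms, so the confounding is partial.
- **That Norway alone draws on daycare.** Study Design says that Italy also recruited from an Alzheimer daycare center, and one set of eligibility criteria applies throughout.
- **That the analysis ignores baseline.** A change score subtracts it. What is missing is conditioning on it, and under randomisation within country that costs precision without causing systematic bias.
- **That chance baseline imbalance at 40:9 is a further harm.** Its standard error is √(1/40 + 1/9) = 0.37 SD, which moves the change-score estimate by (1 − rho) × 0.37, or 0.07 to 0.18 SD for rho 0.8 to 0.5. This is the same loss as in the variance ratio, expressed on another scale, and must not be counted twice.
- **That group sessions undermine the comparison.** EG sessions ran in groups of 4 or 5. At assumed intraclass correlations of 0.05 to 0.10 the between-arm standard error at 40:9 rises by only 2–3%, so this does not belong to the point.

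The objection that a new model chosen after the data are in hand should not displace the stated one stands, and it shapes the fix.

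**Conclusion.** The point holds in a limited form. The stated pooled comparison is biased by design whenever mean change differs between Norway and the other two countries. Under the planned split the size is 0.133 × D: 0.03 to 0.07 SD for assumed differences of 0.25 to 0.5 SD, reaching 0.20 SD only at an assumed 1.5 SD. Whether the realised bias is larger or smaller is unknown until the country-by-arm counts are shown; the documents support neither reading.

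The baseline part concerns efficiency only. ANCOVA would have 10–25% less variance for rho of 0.8 to 0.5 with equal variances, and the saving shrinks if eligibility truncates the baseline. The point is worth correcting because the remedy is nearly free and the effect sizes are meant to be reused, not because it overturns the trial's conclusions.

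**What to change.** Estimate the arm difference from a linear model of the T2 score on arm, country and baseline score, and report the adjusted difference with a 95% CI. Where data are clearly non-normal, add a van Elteren test stratified by country as the rank-based check. Report arm counts by country, both as randomised and as analysed, so that readers can see the realised imbalance.

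The Abstract dates the end of analysis to November 2024, with results still to be published. The model should therefore be labelled as a post hoc change and shown beside the stated tests, not silently substituted for them.

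Cost: one or two sentences, a re-run, and three degrees of freedom (two for country, one for baseline). The limits should be stated openly. Nine controls over three countries average three per country, so there is little within-country information, and a country without controls contributes nothing to the stratified contrast.
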